### Randomization and blinding

2.7

This trial will use centralized block randomization generated by a computer (using the professional statistical software SAS 9.1.3 to assign a randomized group number to allocate the treatment programme to be completed). The randomization programme and the various parameters established during the process are collectively known as the blind code, which will be sealed with the signature of the person who created the randomization programme and will be maintained by a special research group administrator at Hubei Provincial Hospital of TCM who will not participate in the project. Each eligible patient will receive a group number according to the inclusion sequence and will be assigned to the treatment programme with the corresponding number, which will remain the same throughout the trial. Number jumping or selecting is not allowed. Each number is associated with an emergency envelope with the corresponding number, which will be maintained by a principal researcher in each trial unit.

Blinding will be conducted for all patients, evaluators and statisticians. During the trial, only the persons performing the CIA will be aware of the patient's group assignment. The patients will be assigned in a 1:1 ratio to either the CIA group or the sham control group, which will be called A and B, respectively, in the treatment record report. All information will be locked in the database until the statistical analysis is conducted. This study will utilize an independent treatment room and make appointments with the patients directly to ensure that patients from different groups do not communicate.

### Data collection and management

2.8

We use Remote Data Capture (RDC) system to perform data entry. The research assistants will fill out all the electrical CRF through RDC system. Researchers will inspect the eCRF, and signed electrically for the eCRF going into effect. The eCRF and the trace of eCRF revising will be left in the Oracle database.

### Quality control

2.9

This study has a randomized sham-controlled design, to avoid selection bias. The strict control of the inclusion criteria is one of the most important ways to control bias. Formulating specific inclusion criteria and exclusion criteria, strictly restraining the study object within a certain scope and reducing differences contribute to the objectivity of the conclusions. This study will use blinding, i.e., evaluators who are unaware of the characteristics of the groups will evaluate the efficacy and safety; in the summary phase, a third party will perform a blind statistical analysis. Loss of follow-up and adverse effects will be promptly recorded. To ensure a smooth study, specialized clinical training will be provided to all the clinical researchers before the initiation of the trial. Training on the study design and the SOPs will be provided to familiarize each clinical researcher with the studys process and implementation to improve consistency between the internal observations of researchers and the observers to ensure that the conclusions are reliable. Regular team meetings will be held and fully documented. Each centre will design quality control measures and undergo regular inspections to control for centre bias. During the study, the Clinical Research Institute of Hubei Provincial Hospital of TCM will be responsible for quality control, and a specified statistics centre will be responsible for data entry and management.

### Data analysis

2.10

Categorical variables will be described using frequencies and percentages, continuous variables as means or if the data are skewed, as medians interquartile ranges. Primary outcome and secondary outcomes will be evaluated in the intention-to treat population. Missing data will be imputed by multiple imputation (m = 5). Rate of reduction from baseline or change from baseline as the dependent variables will be analyzed using repeated measured mixed effect model with adjustment for baseline level, sex, age, marriage status, drinking and smoking status, family history of obesity, and duration of disease as fixed effect; center effect will be assessed by including indicator of study sites as random effect for G matrix. Differences between the 2 groups at each visit point will be estimated by including treatment group, visit (categorical variable), an interaction between treatment groups and visit as fixed effect. An overall evaluation will be performed to test linear growth tendency by considering visit as continuous variable. Adjusted mean difference and 95% confidence interval will be presented.

Safety assessments will be conducted in the safety analysis set. Incidence of AEs will be compared using Fisher exact method. The changes in laboratory parameters between baseline and 16 weeks will be analyzed using analysis of covariance. McNemar test will be employed to test inconsistency for the grouping information and blinding assessment will be collected on each participant. To assess the effect the missing data on the primary outcome, we will conduct a sensitivity analysis. The data will be transformed into long format for each participant. In the long format, each row is one time point per participant. So each participant will have data in multiple rows. The rows with missing outcome will be excluded from mixed effect model.

All statistical tests will be conducted using a 2-sided type I error rate of 5%. All analyses will be carried out using the SAS software, version 9.4 TS1M6 (SAS Institute Inc, Cary, NC). Data visualization was conducted by using R version 3.5.1 software (The R Foundation for Statistical Computing, Vienna, Austria (http://www.r-project.org/) with the R packages ggplot2.

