#### Primary outcome

2.5.1

The primary outcome measurement of this study will be the rate of waistline reduction compared with the baseline. Evaluations will be conducted at weeks 0, 4, 8, 12, 16, 28, and 40. The waistline is the simplest and most practical index to measure the amount of fat accumulated in the stomach (central obesity). The distribution of fat in the body, especially the accumulation of fat in the stomach, has a close relationship with obesity-related diseases.

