### Sample size estimation

2.6

Based on a review of the literature, clinical experience and discussion among clinical experts, we anticipated 7% waistline reduction at 16 weeks in the CIA group and 2% reduction in the sham CIA group. Eighty six participants per group was required based on:

1.a mean clinically relevant difference of 5% (2% reduction in the sham CIA group), with a pooled standard deviation (SD) of 8.1%;2.2-sided at 5% and 1- at 80%.

Assuming 20% attrition rate, we plan to enrol a total of 216 participants (108 per group).

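### Five imputations give a valid primary analysis but leave avoidable simulation noise of about 13% to 18% of the standard error; a larger number would remove most of it at no real cost

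*Protocol article*

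**What the plan says.** Section 2.10 (Data analysis) assigns the primary and secondary outcomes to the intention-to-treat population and then states "Missing data will be imputed by multiple imputation (m = 5"). The number is fixed in the text, not left open. The analysis model is a repeated-measures mixed model with treatment, visit and their interaction. For the primary outcome, section 2.5.1 has the visit schedule: "Evaluations will be conducted at weeks 0, 4, 8, 12, 16, 28, and 40".

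Section 2.6 (Sample size estimation) shows how much loss is expected: "Assuming 20% attrition rate, we plan to enrol a total of 216 participants (108 per group").

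Section 2.10 also plans a sensitivity analysis of the primary outcome for missing data, using the same kind of model without imputation: "The rows with missing outcome will be excluded from mixed effect model".

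**The concern.** Five imputations are usually defended by relative efficiency, which is about 96% to 98% here. That figure describes the average loss of variance. It does not say how far the estimate and p-value from one data set would move if the imputations were drawn again.

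If that movement is a noticeable part of the standard error, the primary estimate, its interval and its p-value partly reflect the random draw and not only the data. A result close to the 5% threshold could then be questioned as depending on the seed. This component of error can be made small by computing alone, without more patients or data.

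**Working it through.** **Inputs from the documents**
- Imputations: m = 5 (section 2.10).
- Attrition: 20%, with 108 randomised per group (section 2.6).
- Effect: "a mean clinically relevant difference of 5" percentage points; spread: "with a pooled standard deviation (SD) of 8.1" points (section 2.6).
- Evaluable per group: 86 (section 2.6). Allocation is 1:1 (section 2.7).

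**Assumption not in the documents:** FMI of 0.10 to 0.20, with 0.05 as a low case. Attrition of 20% is not the same as an FMI of 0.20, because earlier visits recover part of the lost information.

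**The plan's own figures.** 86/(1 − 0.20) = 107.5, so 108 per group is reproduced. The 86 itself is not: 2 × (1.96 + 0.84)² × 8.1²/5² = 41.2, that is 42 per group (43 with the t distribution). This is a separate matter. The percentages of the standard error below do not depend on it, and 86 evaluable per group is what 108 with 20% loss delivers.

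**Step 1. Standard error (SE).** SE = 8.1 × √(2/86) = 1.235 points. The planned effect is at z = 5/1.235 = 4.05.

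**Step 2. Simulation noise.** By Rubin's rules the between-imputation share of the total variance is B/T = FMI/(1 + 1/m). The noise relative to the SE is √(B/(mT)). Relative efficiency is 1/(1 + FMI/m).

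| FMI | m | B/T | Noise / SE | Noise, points | Relative efficiency |
|---|---|---|---|---|---|
| 0.05 | 5 | 0.042 | 0.091 | 0.11 | 0.99 |
| 0.10 | 5 | 0.083 | 0.129 | 0.16 | 0.98 |
| 0.20 | 5 | 0.167 | 0.183 | 0.23 | 0.96 |
| 0.10 | 50 | 0.098 | 0.044 | 0.05 | 0.998 |
| 0.20 | 50 | 0.196 | 0.063 | 0.08 | 0.996 |

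**Step 3. A near-threshold data set.** Suppose the data would give z = 2.1 with unlimited imputations, a difference of 2.1 × 1.235 = 2.6 points. The share of seeds below 1.96 is Φ((1.96 − 2.1)/r), where r is the noise/SE ratio:
- m = 5: Φ(−1.08) = 14% at FMI 0.10; Φ(−0.77) = 22% at FMI 0.20.
- m = 50: about 0.1% and 1%.

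**Step 4. Overall chance of a changed decision.** Let z, the statistic with unlimited imputations, be normal with mean μ and unit variance. Add independent noise with standard deviation r. The probability that z and z plus noise lead to different decisions at ±1.96, integrated over z, is:

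| Expected z (μ) | m = 5, FMI 0.10 to 0.20 | m = 50, FMI 0.10 to 0.20 |
|---|---|---|
| 4.05 (planned effect) | 0.5% to 0.7% | 0.2% |
| 0 (null) | 1.2% to 1.8% | 0.4% to 0.6% |
| 1.96 (worst case) | 4% to 6% | 1.4% to 2.0% |

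**Step 5. Check by simulation.** Setting: 108 per arm, 22 per arm missing, SD 8.1, normal-model imputation, and the same data re-imputed many times. The correlation of the missing value with an earlier visit was assumed to be 0, 0.5 or 0.8. With m = 5 the seed alone moved the estimate with an SD of 0.23, 0.21 and 0.16 points, about 13% to 20% of the SE. For a data set with p near 0.05, the middle 95% of p-values ran from 0.016 to 0.164 (correlation 0) and from 0.028 to 0.106 (correlation 0.8). With m = 50 these ranges were 0.038 to 0.075 and 0.043 to 0.065. At the planned effect every run was significant.

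**The case against.** The strongest case for leaving the plan alone has five parts.

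- **Validity.** Rubin's rules add (1 + 1/m)B to the variance and adjust the degrees of freedom, so the interval is already widened for finite m. There is no bias and no loss of type I error control. This stands in full.
- **Rarity.** The 14% to 22% applies only once the data have landed at z = 2.1. That is about half the planned effect. The unconditional figures in step 4 are the fair measure, and they are small. This stands.
- **A check that needs no seed.** The observed-rows mixed model uses all observed visits and has no simulation error. With a compatible imputation model it approximates the answer from very many imputations. It would therefore tend to expose a p-value that owed its side of 0.05 to the draw. This stands, but that model is the sensitivity analysis and does not steady the reported primary result.
- **The assumed FMI.** The 20% has no stated time point and follow-up runs to week 40, so loss by week 16 may be lower; 0.20 is the pessimistic end. This also stands. At an FMI of 0.05 the noise is still 9% of the SE.
- **The seed.** A reader might infer that two analysts following the plan would report p-values on opposite sides of 0.05. The article does not support this. A seed, or a check of simulation error, is commonly set in the statistical analysis plan, which is not shown, and section 2.9 gives the blinded analysis to one third party. Its absence here is no finding.

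What survives is narrower: the number 5 is written into the plan, and a larger one is better at almost no cost.

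**Conclusion.** The point holds as an optional improvement in precision and reproducibility. With m = 5 the primary estimate carries simulation noise of about 13% to 18% of its SE at an assumed FMI of 0.10 to 0.20. For comparison, 0.16 to 0.23 points is small against the planned 5.

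A reader might go further and conclude that m = 5 makes the primary analysis unreliable or invalid. The documents do not support that: at the planned effect the decision would change in fewer than 1 trial in 100, and at worst in about 4 to 6 in 100.

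The sizes rest on the assumed FMI, on 86 evaluable per group with SD 8.1, and on a normal approximation. The simulation in step 5 agrees with them.

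**What to change.** In section 2.10, replace m = 5 with a larger number, for example m = 50. This brings the noise to about 4% to 6% of the SE. Fifty is an example and not a threshold: at an FMI of 0.20, m = 20 already brings the noise to about 10% of the SE (√(0.190/20) = 0.098). No number of imputations settles a result that lies almost exactly at 0.05, but a larger number narrows the range of p-values that the draw can produce.

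The cost is one number in the text and negligible computing time. Nothing else in the analysis, and no data or patients, would be affected.

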#### Withdrawal from the study

2.3.4

1.A specialist physician at each centre responsible for evaluating serious adverse effects during the study decides to withdraw the patient from the study2.Severe complications or other severe diseases necessitating emergency measures3.Participants decision to withdraw from the study

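### The one sensitivity analysis named for missing data makes the same missing-at-random assumption as the primary analysis, so it cannot show the effect of dropout that is not at random

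*Protocol article*

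**What the plan says.** All references are to the protocol article.

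- Data analysis (2.10), population: "Primary outcome and secondary outcomes will be evaluated in the intention-to treat population".
- Data analysis, handling of missing values: "Missing data will be imputed by multiple imputation (m = 5"). The imputation model and the assumed missingness mechanism are not given.
- Data analysis, model: rate of reduction or change from baseline "will be analyzed using repeated measured mixed effect model with adjustment for baseline level, sex, age, marriage status" and further covariates, with group, visit and their interaction.
- Data analysis, aim of the check: "To assess the effect the missing data on the primary outcome, we will conduct a sensitivity analysis".
- Data analysis, content of the check: the data are put in long format, one row per participant and time point, and "The rows with missing outcome will be excluded from mixed effect model".
- Sample size estimation (2.6): "Assuming 20% attrition rate, we plan to enrol a total of 216 participants (108 per group").
- Withdrawal from the study (2.3.4): three routes out. These are a decision by the specialist physician who is "responsible for evaluating serious adverse effects during the study decides to withdraw the patient from the study", severe complications or diseases that need emergency measures, and the participant's own choice.
- Sham control group (2.4.2): an empty needle at equivalent depth, with no catgut embedded.

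**The concern.** A sensitivity analysis for missing data should change the assumption that the data cannot test. Here the primary analysis fills gaps from the observed data, and the check leaves the gaps and lets the likelihood of the mixed model deal with them. Both assume that, given what was observed, patients who left would have gone on like those who stayed. They estimate the same quantity from largely the same information, so they will nearly always agree, whether or not the assumption is true.

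The assumption could plausibly fail in this trial. The plan budgets for one patient in five leaving. Patients who see no benefit may leave by choice, and a reaction to embedded catgut can occur in one arm only. If poor responders leave the CIA arm selectively, the estimated benefit is too large, and the planned check would report it as robust.

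**Working it through.** **1. The plan's own attrition figure.** 86 / (1 − 0.20) = 107.5, rounded up to 108 per group, so the attrition step reproduces. (The 86 per group does not follow from the stated inputs. A difference of 5, SD 8.1, two-sided 5% and 80% power give 42 to 43 per group, or about 86 in total. That is a separate matter. A larger sample improves precision but does not remove bias.)

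**2. Do the two planned analyses separate when the assumption fails?** Simulation with 108 per arm, six post-baseline visits, a true week-16 difference of 5 points, SD 8.1, about 20% dropout after week 8, and 150 runs. Assumed, not in the documents: within-patient correlation 0.6, the visit profile, and models without covariates. Sham dropout was completely at random.

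- CIA dropout driven by the observed week-8 value: observed-rows model 4.98, multiple imputation (m = 5) 4.97.
- CIA dropout driven by the unseen week-16 value: 6.45 and 6.45.

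The Monte Carlo standard error is about 0.10. In the second case both are too high by 6.45 − 5 = 1.45 points, or 1.45 / 5 = 29%. Across runs the two estimates correlate at 0.99 and differ by 0.15 points on average, so their agreement carries no warning.

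**3. Size at the planned effect.** Inputs from Sample size estimation: 7% reduction with CIA, 2% with sham, 20% missing. Sham dropouts are taken to follow the sham mean.

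- CIA dropouts end like sham patients: 0.8 × 7 + 0.2 × 2 − 2 = 4.0.
- CIA dropouts return to baseline: 0.8 × 7 + 0.2 × 0 − 2 = 3.6.

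In general, effect = 5 − (missing share in the CIA arm × shortfall). The documents do not give attrition by arm, so a range is shown for shortfalls of 2, 5 and 7 points:

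- 10% missing: 4.8, 4.5, 4.3
- 20% missing: 4.6, 4.0, 3.6
- 30% missing: 4.4, 3.5, 2.9

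**4. Significance.** With 86 observed per arm, SE = 8.1 × √(2/86) = 1.24, held fixed as a simplification. An estimate of 5 has a 95% interval of 2.58 to 7.42. Then 4.0 / 1.24 = 3.2 and 3.6 / 1.24 = 2.9, both above 1.96.

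**5. Tipping shortfall at 20% missing,** (estimate − 1.96 × SE) / 0.2, using the unrounded SE of 1.235:

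- estimate 5: (5 − 2.42) / 0.2 = 12.9 points
- estimate 3: (3 − 2.42) / 0.2 = 2.9 points
- estimate 2.5: (2.5 − 2.42) / 0.2 = 0.4 points

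**6. Number of imputations.** If the fraction of missing information is taken as 0.2, relative efficiency is 1 / (1 + 0.2/5) = 96% with m = 5 and 1 / (1 + 0.2/50) = 99.6% with m = 50. Repeated imputation of one simulated data set with an estimate near 2.6 (correlation 0.7 assumed, 400 seeds) gave a central 95% range of p from 0.014 to 0.078 with m = 5 and from 0.025 to 0.044 with m = 50. At the planned 5 points the choice hardly matters.

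**The case against.** The strongest reply has four parts.

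- **The check is not empty.** Refitting without imputation shows whether the result depends on the imputation model and on only five imputations. This stands. A reader might infer that the check says nothing at all about 20% attrition, and that would go too far. What it cannot show is attrition that is not at random.
- **An article leaves detail to the analysis plan.** The missing-at-random assumption is inferred, because the article does not state the imputation model. The absence of a tipping-point analysis would not by itself be a finding. But the article does define its check and states the aim, and a check of this kind cannot meet that aim in full. Auxiliary variables in the imputation would not change this.
- **Dropout that differs by arm is possible, not shown.** Both arms are needled to similar depth and patients are blinded. A reader might infer from section 2.3.4 that patients with adverse effects in general are withdrawn. The text does not say so. It covers serious adverse effects at a specialist's decision, severe complications or diseases, and the participant's choice, while reactions such as local induration or haematoma are recorded under Safety assessment. Nor does the article say that measurement stops after withdrawal. No rate of serious events is given.
- **The conclusion survives at the planned effect.** This also stands: a tipping shortfall of 12.9 points exceeds the whole 7% reduction expected with CIA.

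**Conclusion.** The point holds in a limited form. The only missing-data sensitivity analysis that the article names shares the missing-at-random assumption of the primary analysis. It is therefore a check on the imputation step and not on the assumption that matters most.

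At the planned effect the plausible loss is 1.0 to 1.4 points of 5, which does not change significance. The gap matters if the observed effect is smaller: at 3 points, a shortfall of 2.9 points among the missing CIA patients is enough to lose significance. These figures assume 20% missing in the CIA arm, sham dropouts at the sham mean, SD 8.1 and a fixed standard error. The 1.45-point bias in the simulation also depends on the assumed correlation and dropout mechanism, so it shows that the two analyses fail together and does not forecast the size of the bias.

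The small number of imputations is a minor point of reproducibility. The documents do not support a reading that the trial's result would be overturned, or that the withdrawal rule itself is at fault.

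**What to change.** In Data analysis (2.10):

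- Keep multiple imputation as primary, state that it assumes missing at random, and keep the observed-rows model as a secondary check on the imputation step.
- Add two analyses of waistline reduction at week 16, the visit on which the sample size is based. The first is a control-based imputation, in which missing CIA outcomes are drawn from the sham distribution. The second is a delta-adjusted tipping-point analysis in the CIA arm, reporting the shortfall at which significance is lost so that readers can judge whether it is plausible.
- Raise m, for example to 50, and record the seed. This is a small gain at no real cost.

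Section 2.3.4 needs no rewrite for this purpose. At most, the sponsor should clarify whether outcomes are still measured, with consent, after withdrawal, because that determines how much is missing.

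The cost is a few sentences in the analysis plan, modest programming and additional reporting. The primary estimate, the sample size and the treatment rules do not change.

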## Discussion

3

For people with simple obesity, acupuncture treatment should be conducted every day or every other day. Because people are often busy with life and work, it is difficult for them to follow the instructions of physicians. CIA changes the pattern of acupuncture treatment in that certain embedded stimulants can stimulate acupoints for about 2 weeks, which significantly increases patient compliance.^[31]^ According to relevant reports, the effect of CIA is similar to that of pricking blood therapy.^[32]^

In our previous studies, it was observed that the body weight, BMI, and fasting blood glucose level decreased after CIA integrated with diet and exercise in the patients with simple obesity.^[33,34]^ However, previous trials were limited by their small size and lack of blinding, and the results were insufficient to determine whether there was a placebo effect; therefore, we designed this study to demonstrate the efficacy and safety of treating simple obesity with CIA. This study follows the guidelines of the STRICTA,^[35]^ the Effectiveness Guidance Document (EGD),^[36]^ and the Consolidated Standards of Reporting Trials (CONSORT).^[37]^ We choose common obesity indexes, including waistline, weight, BMI, hipline, WHR and BFP, scales for assessing psychological status, including the HAD and the SES, scales for assessing the quality of life, including the IWQOL-Lite and the SF-36 as the outcome measurements of efficacy evaluation. For the safety evaluation, general physical examination items (blood pressure, heart rate, routine blood tests, etc.), the incidence of adverse events, and the receptivity to catgut implantation at acupoints will be analyzed.

There are no previous studies of the safety and efficacy of CIA for the treatment of simple obesity using sham control. Referring to previous sham-controlled studies investigating acupuncture for simple obesity and considering the use of blinding and the place of the sham control, the acupoints in the sham control group will be located 1 cun (≈20 mm) from the locations used in the CIA group. The sham acupoints cannot be located at any real acupoints or in the meridians of the body, and no catgut will be embedded during the operation. Due to the characteristics of CIA, we believe that this procedure exhibits adequate blinding. To objectively evaluate the clinical effects of treating simple obesity with CIA, the patients will be unaware of whether they will receive CIA. For both groups, we will also consider ethics. We will provide a basic treatment with diet and exercise to both the treatment group and the control group. If the treatment with CIA has no benefits over sham catgut implantation, the patients will still lose weight and develop good eating and exercise habits.

The instrument for CIA used in this study will be a disposable sterile microinvasive needle, which can improve the quality of catgut implantation and effectively prevent nosocomial infection. According to previous clinical experience, it takes about 2 weeks to completely absorb collagen catgut; therefore, the interval between the 2 treatments will be 2 weeks. The acupoints used in Group A and Group B are alternated based on clinical evidence. To ensure the safety and reliability of this study, all acupuncturists and operators will receive specialized training.

In summary, the primary objective of this study is to demonstrate the safety and efficacy of treating simple obesity with CIA. We expect that this study will provide favourable evidence for the treatment of simple obesity with CIA.
